## Abstract

**Background:**

Persistent atrial fibrillation frequently shows multiple different electrophysiological mechanisms of induction. This heterogeneity causes a low success rate of single procedures of ablation and a high incidence of recurrence. Surgical ablation through bilateral thoracotomy demonstrates better results after a single procedure. Prospective observational studies in inhomogeneous populations without control groups report a remarkable 90% of success with hybrid or staged procedures of surgical ablation coupled with catheter ablation. In this trial, we will examine the hypothesis that a staged approach involving initial minimally invasive surgical ablation of persistent atrial fibrillation, followed by a second percutaneous procedure in case of recurrence, has a higher success rate than repeated percutaneous procedures.

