**Methods/Design:**

This is a controlled (2:1) randomized trial comparing use of a percutaneous catheter with minimally invasive transthoracic surgical ablation of persistent atrial fibrillation. The inclusion and exclusion criteria, definitions, and treatment protocols are those reported by the 2012 Expert Consensus Statement on catheter and surgical ablation of atrial fibrillation. Patients will be randomized to either percutaneous catheter (*n* = 100) or surgical (*n* = 50) ablation as the first procedure. After 3 months, they are re-evaluated, according to the same guidelines, and receive a second procedure if necessary. Crossover will be allowed and data analyzed on an “intention-to-treat” basis. Primary outcomes are the incidence of sinus rhythm at 6 and 12 months and the proportions of patients requiring a second procedure.

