In the present trial, we examine the hypothesis that a staged approach involving minimally invasive surgical ablation of persistent atrial fibrillation, followed by a second percutaneous procedure in cases of recurrence, will have a success rate at 12 months higher than repeated percutaneous procedures. According to the recently published European guidelines on surgical ablation of AF alone, we will select patients with a class IIb indication to surgery and use the class I bipolar radiofrequency as the energy source for the ablation [12].

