## Methods

The overall hypothesis of this study is that an initial surgical procedure has a higher probability of success than an initial percutaneous ablation, and therefore, fewer patients will be submitted to a second ablation. The proposed therapies are currently accepted and considered Class II indications in the current European Society of Cardiology [13] and European Association of Cardiothoracic Surgery [12] guidelines for the treatment of PeAf. As such, their comparison complies with the Declaration of Helsinki for the Ethical Principles of Medical Research in human subjects. The Ethics Committee of the University of Magna Grecia in Catanzaro (Italy) gave full approval to the study without conditions. No external financial support exists. Full reimbursement of the cost of the therapies has already been granted by the Italian National Health System.

All participants will be required to sign an informed consent to adhere to the study. The Surgical Staged Approach (SSA) strategy consists of an initial minimally invasive surgical ablation, followed by a percutaneous catheter ablation if necessary. To avoid any possible bias introduced by the difference in surgical techniques, we will use only the bipolar radiofrequency using the Estech cobra fusion ablator (Estech is a Market brand of Atricure Inc West Chester 45069 Ohio USA) introduced through a right minimal thoracotomy. The control group will receive the current standard strategy of PCA. In the case of recurrence of the AF, the second procedure will be either percutaneous or surgical. The inclusion criteria and the protocols for managing the pharmacologic and anticoagulant therapy, the description of the surgical approach, and the technique of the percutaneous ablation are those indicated by the 2012 HRS/EHRA/ECAS expert consensus statement on catheter and surgical ablation of AF [12] and the European Guidelines for the treatment of lone AF [13].

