### Staged surgical ablation group

Fifty patients will be randomized to surgical ablation of AF. The ablation procedure will be performed with the use of Estech cobra fusion, according to the manufacturer’s instructions and to the commonly described techniques [10,12,15]. Up to three applications will be allowed to ablate the left atrial box. Bidirectional block will be checked, and reasons for not obtaining it will be noted. Inducibility of AF at the end of the procedure will be recorded. Cardioversion will be allowed to restore SR. At the end of the procedure, the patient will be awakened and transferred to the ward. An interval of 3 months will be allowed after the initial ablation procedure, as per the Heart and Rhythm European Society Association/European Heart Rhythm Association/European Cardiac Arrhythmia Society expert consensus statement [13]. During this period, the recurrences of AF, atrial tachycardias, and atrial flutter will not be counted toward the primary or secondary end points. Antiarrhythmic medications may be continued for the first 3 months to avoid early recurrences. At 3 months, they must be stopped to assess recurrences. For patients continuing to have recurrence controlled by the therapy, it will be left to the preference of the investigator to continue the medical therapy or to refer the patient for a PCA.

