### Assessment of recurrence

The recurrence will be assessed by clinical follow-up at 1, 3, 6, 9, and 12 months with 12-lead ECG + 24 Holter monitoring. Transthoracic echocardiography will be also performed to record the presence of an atrial contraction in case of sinus rhythm. Quality of life will be assessed by a modified 36-item Short Form Health Survey and the Euro 5D questionnaire. The primary outcomes include the freedom from AF at 12 months, as detected by a 12-lead ECG and a 24-hour Holter examination after 3, 6, and 9 months of follow-up, and the occurrence of a second ablation procedure. The secondary outcomes include the duration of the procedures, freedom from any documented atrial arrhythmia, incidence of procedural complications, any late complication related to the procedures, and quality of life.

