### Statistical analysis

Randomization will be performed by using currently available computer software. Sample size is based on the hypothesis that the success rate of the first procedure will be approximately 70% for the surgical cases and 35% to 40% for the PCA cases. At the end of the interventions, the number of patients in SR should be equivalent in the two groups, whereas the proportions of those submitted to a second procedure, either percutaneous or surgical, should differ significantly. Variables will be analyzed with an intention-to-treat method. The three possible results of this study are described in Table 1. A flow chart depicting the most favorable result in which the power of the test is 98% is shown in Figure 1. Data will be expressed as mean ± SD and 95% confidence limits, as appropriate. Comparisons between patient groups will be performed with the Mann–Whitney test for continuous variables and the χ^2^ test for categoric variables. The *z* test and the odds ratio will be used for differences between proportions of patients receiving repeated procedures in the two groups. A value of *P* < 0.05 will be considered statistically significant. Time-to-event distributions will be estimated by the Kaplan-Meier method and compared with the log-rank test. The Cox proportional hazards model will be used to identify independent risk factors for recurrences. Stepwise selection procedure will be adopted. A value of *P* < 0.05 will be considered significant for variable entry for stepwise selection. Analyses are performed with the SPSS 18.0 software package (SPSS, Inc, Chicago, IL, USA).

**Table 1 T1:** Anticipated results for different success rates of first PCA procedure

**% of SR in the PCA group after first procedure**	**35%**	**45%**	**50%**
**χ**^ **2 ** ^**test for first procedure**	*P* < 0.0001	*P* = 0.007	*P* = 0.03
Power of the test	99%	84%	65%

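### The Background hypothesises higher 12-month success with the staged strategy, while the statistics section expects equal final rhythm and powers only the first procedure; 12-month rhythm needs one stated hypothesis

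*Protocol article*

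**What the plan says.** The protocol article states the hypothesis in three places and a planning expectation in a fourth.

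- **Abstract, Background:** the staged approach "has a higher success rate than repeated percutaneous procedures".
- **Background, last paragraph:** the staged approach "will have a success rate at 12 months higher than repeated percutaneous procedures".
- **Methods, opening paragraph (the overall hypothesis):** "an initial surgical procedure has a higher probability of success than an initial percutaneous ablation, and therefore, fewer patients will be submitted to a second" (that is, a repeat procedure).
- **Statistical analysis:** at the end of the interventions "the number of patients in SR should be equivalent in the two groups", while the proportions having a second procedure should differ significantly.

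Rhythm is a primary outcome in both places that list outcomes. Assessment of recurrence has "The primary outcomes include the freedom from AF at 12 months", together with the occurrence of a second ablation. The Abstract has "Primary outcomes are the incidence of sinus rhythm at 6 and 12 months and the proportions of patients requiring a second procedure".

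The sample size rests on the assumption that "the success rate of the first procedure will be approximately 70% for the surgical cases and 35% to 40% for the PCA cases". Table 1 gives power, relative risk, odds ratio and the difference in second-procedure fractions for first-PCA success of 35%, 45% and 50%. It has no row for 12-month rhythm. The tests named for comparing the groups are chi-square, z, Mann–Whitney and log-rank, with P < 0.05 as the threshold.

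**The concern.** Superiority and equivalence of the same outcome cannot both be the trial's expectation. The Methods hypothesis, the statistics section and Table 1 agree with each other: surgery first should succeed more often at the first attempt and so spare second procedures. The Abstract and Background are the outliers, because they promise a better rhythm result at 12 months.

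Two things are at stake. First, with both expectations in print, either rhythm result could be presented as confirmation: a significant difference would fit the Background, and no significant difference would fit the statistics section. Second, the attractive overall conclusion is similar rhythm with fewer procedures. Its first half has no margin and no decision rule, and the tests named cannot establish similarity.

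**Working it through.** **Inputs.** n = 100 PCA and 50 surgery (the two treatment-group sections); alpha 0.05. Sidedness is not stated, but two-sided reproduces the published power. First-procedure success is 70% for surgery and 35%, 45% or 50% for PCA (Statistical analysis, Table 1). Final-rhythm rates and margins are not stated, so those below are assumptions shown as a range. The Background reports 74% after one combined PCA, 88% after repeated PCA and 90% for a hybrid approach. These are results of other series, not planning rates.

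**1. Reproduce the plan's own power.** Two-proportion test with pooled null variance and no continuity correction:

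power = Φ[(|d| − 1.96·SE0) / SE1], where SE0 = √[p̄(1−p̄)(1/100 + 1/50)] and SE1 = √[p1(1−p1)/100 + p2(1−p2)/50].

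For 35% versus 70%: p̄ = (35 + 35)/150 = 0.4667, SE0 = 0.0864, SE1 = 0.0805, power = 98.8%. For 45% it is 83.8% and for 50% it is 65.1%. Table 1 gives 99%, 84% and 65%, so it reproduces. These figures apply to first-procedure success and, through one minus that rate, to second procedures (0.65, 0.55 or 0.50 versus 0.30). They say nothing about final rhythm.

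**2. Superiority of 12-month rhythm (the Background hypothesis).** Exact power of the uncorrected chi-square test, n = 100/50:

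| PCA | Surgery first | Power |
|---|---|---|
| 88% | 90% | 5.7% |
| 80% | 90% | 34% |
| 74% | 90% | 67% |
| 57.8% | 80.5% | 82% |

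The last row assumes that every first failure has a second PCA that succeeds 35% of the time: PCA 1 − 0.65² = 0.578; surgery 0.70 + 0.30 × 0.35 = 0.805.

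**3. Equivalence of 12-month rhythm (the statistics-section expectation).** Two one-sided tests at 5% each, equal true rates p, margin m:

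SE = √[p(1−p)(1/100 + 1/50)]; power = 2Φ(m/SE − 1.645) − 1, set to 0 if negative.

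| Rate in both groups | SE | 95% CI half-width (1.96·SE) | m = 10 points | m = 15 | m = 20 |
|---|---|---|---|---|---|
| 70% | 0.0794 | 15.6 points | 0% | 19% | 62% |
| 80% | 0.0693 | 13.6 | 0% | 40% | 79% |
| 88% | 0.0563 | 11.0 | 10% | 69% | 94% |
| 90% | 0.0520 | 10.2 | 22% | 79% | 97% |

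Example at 88% and m = 10: 0.10/0.0563 − 1.645 = 0.132, and 2Φ(0.132) − 1 = 0.105.

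**4. What a non-significant difference test would show.** If true rates were 88% for PCA and 78% for surgery first, the exact chi-square power is 37.4%, so the test is non-significant 62.6% of the time. At 80% versus 70% it is non-significant about 71% of the time.

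**The case against.** The strongest reply has five parts.

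- **The expectation of equivalence is a planning remark, not a test.** This stands. A reader might infer that a non-significant P value will be taken as equivalence. The article nowhere says so, and it also promises 95% confidence limits where appropriate. What can be said is that the tests named would not support an equivalence statement if one were made.
- **The Methods section already states the powered hypothesis.** This stands too. That hypothesis, the sample size and one primary outcome are coherent, so the defect is the mismatch with the Abstract and Background, plus a primary rhythm outcome with no stated power.
- **The trial may be able to show either result.** A reader might conclude that equivalence is beyond a trial of this size, or that superiority power is negligible. Neither holds in general. Equivalence power reaches 94–97% at a 20-point margin with rates of 88–90%. The 6% superiority figure belongs to one pair of background rates, and the 90% in that pair comes from a hybrid procedure that the Discussion distinguishes from the staged one used here.
- **The two statements may refer to different times.** The statistics section speaks of the end of the interventions rather than 12 months. But rhythm after any second procedure is what the 12-month outcome captures, and the article gives no other expectation for it.
- **A margin may sit in a fuller document.** It may, and its absence from an article is not itself the fault. But no fuller document can make both directions true for the same outcome.

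**Conclusion.** The point holds as a contradiction within the article. The Abstract and Background hypothesise higher success with the staged strategy; the statistics section, in line with the Methods hypothesis and the sample size, expects equal final rhythm and fewer second procedures. As written, neither superiority nor equivalence of 12-month rhythm has a stated power, and a non-significant difference test would not support equivalence.

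The size depends on rates and margins that the article does not give. Over the assumed values, superiority power ranges from about 6% to 82%. Equivalence power ranges from 0% (10-point margin, 70–80% in rhythm) to 97% (20-point margin, 90% in rhythm). That spread is why the hypothesis and any margin must be fixed before data review. The powered comparison of first-procedure success and second procedures is not in question. The correction is still needed, because it decides what the trial may conclude on a primary outcome.

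**What to change.** 1. Make the hypothesis in Methods and Statistical analysis the single confirmatory one: surgery first gives higher first-procedure success and therefore fewer second procedures. Reword the Abstract and the last paragraph of the Background to match.
2. Report the 12-month rhythm difference with its 95% CI, and state the precision to expect: a half-width of about 10 to 16 points for rates from 90% down to 70%.
3. State that no claim of equivalence, or of being no worse, will rest on a non-significant P value. Allow such a claim only if the CI excludes a margin justified and fixed before data review.

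The cost is a change of wording, one reporting rule and a more modest claim about 12-month rhythm. No patients are added.

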**Difference between proportions**			
Fraction of second procedures in the two groups	0.65-0.30	0.55-0.30	0.50-0.30
Difference between fractions	0.35	0.25	0.2
95% confidence interval of difference	0.1 to 0.5	0.1 to 0.4	0.0 to 0.3

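### The second-ablation primary outcome counts procedures received, and the protocol has no common rule for patients who never get a second procedure; the direction of the resulting bias is unknown

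*Protocol article*

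**What the plan says.** The protocol article's Assessment of recurrence section lists two primary outcomes: freedom from AF at 12 months, "and the occurrence of a second ablation procedure". The Abstract words the second one as "the proportions of patients requiring a second procedure".

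The Statistical analysis section gives the test: "The *z* test and the odds ratio will be used for differences between proportions of patients receiving repeated procedures in the two groups". It also states: "Variables will be analyzed with an intention-to-treat method". Kaplan-Meier and log-rank methods are listed there too, but are not tied to a named endpoint.

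Two passages deal with recurrence that does not lead to a second ablation:

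- **Percutaneous catheter ablation group:** after the blanking period the investigator may choose rate control, and that choice is counted as a failed repeated procedure.
- **Staged surgical ablation group:** where recurrence is controlled by drugs, the investigator may continue them or refer the patient for PCA. No counting rule is attached.

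**The concern.** Need for a second ablation and receipt of one are different quantities. They part company for patients who cannot, or do not, go on to another procedure: those who die, leave before re-evaluation, never have the allocated first ablation, or recur and are managed without ablation. If all randomised patients form the denominator and only performed procedures form the numerator, each of these patients lowers the arm's second-procedure rate.

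The trial's argument is that surgery first means fewer second ablations. The arms are thoracotomy and catheter ablation, so equal refusal and loss cannot be taken for granted. The rate-control rule shows that failure without a second procedure was foreseen, but only in one arm. It is also unclear whether such a patient enters the numerator of the z test. If so, PCA failures managed without ablation are counted and their surgical counterparts are not.

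**Working it through.** **Inputs.** Allocation (Abstract): "Patients will be randomized to either percutaneous catheter (*n* = 100) or surgical (*n* = 50) ablation as the first procedure". Significance level: "A value of *P* < 0.05 will be considered statistically significant"; two-sided is assumed here because it reproduces Table 1. Design assumption: "success rate of the first procedure will be approximately 70% for the surgical cases and 35% to 40% for the PCA cases". Table 1's row "Fraction of second procedures in the two groups" gives 0.65, 0.55 and 0.50 for PCA against 0.30 for surgery, that is 65, 55 or 50 of 100 against 15 of 50. No loss, refusal or death rate is given, so the number of affected patients is varied.

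**Step 1: reproduce Table 1's power.** With s0 = √[p̄(1 − p̄)(1/100 + 1/50)] and s1 = √[p1(1 − p1)/100 + p2(1 − p2)/50], power = Φ[(|p1 − p2| − 1.96·s0)/s1].

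For the 50% column, p̄ = 65/150 = 0.433, s0 = 0.0858 and s1 = 0.0819. Then (0.20 − 0.168)/0.0819 = 0.39, and power is 65.1%. The 35% and 45% columns give 98.8% and 83.8%. Table 1 states 99%, 84% and 65%, so it is reproduced.

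**Step 2: what Table 1 assumes.** Each second-procedure fraction is one minus first-procedure success: 1 − 0.35 = 0.65, 1 − 0.45 = 0.55, 1 − 0.50 = 0.50, and 1 − 0.70 = 0.30. That equality holds only if every first failure receives a second procedure and every patient is observed.

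**Step 3: recount surgical patients as events, PCA unchanged.** z = (pPCA − pSurg)/s0, with the pooled proportion recalculated each time. In the 50% column:

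- 15/50 v 50/100: z = 0.20/0.0858 = 2.33, P = 0.020
- 16/50: z = 2.09, P = 0.036
- 17/50: z = 1.86, P = 0.063

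Number of surgical patients who must be recounted before P exceeds 0.05:

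| PCA first-procedure success | Counts before recounting | P before | Patients needed | P after |
|---|---|---|---|---|
| 50% | 15/50 v 50/100 | 0.020 | 2 | 0.063 |
| 45% | 15/50 v 55/100 | 0.004 | 5 | 0.083 |
| 40% (in text, not a Table 1 column) | 15/50 v 60/100 | 0.0005 | 7 | 0.064 |
| 35% | 15/50 v 65/100 | 0.0001 | 10 | 0.077 |

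With the Yates correction, which matches Table 1's P values of 0.007 and 0.03, the numbers needed are 1, 4, 6 and 9.

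**Step 4: exclude the two patients instead.** 15/48 v 50/100 gives P = 0.031, still significant. Five exclusions (15/45) give P = 0.062.

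**Step 5: equal loss in both arms, counted as no event.** At 10% loss in the 50% column the fractions become 0.50 × 0.9 = 0.45 and 0.30 × 0.9 = 0.27. The difference falls from 0.20 to 0.18 and power from 65.1% to 57.1%. At 2% and 5% loss, power is 63.5% and 61.1%.

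**The case against.** The strongest reply is that the article never says a patient who dies, withdraws or is never ablated is a success. It names a principle and a test, and handling of losses is commonly left to a full protocol or SAP that is not shown. This stands in part: a missing dropout policy alone would not be a finding. What remains is a measure the article does fix, a proportion receiving a procedure, and a counting rule it states for one arm only.

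A reader might infer that two surgical patients can decide the trial. The documents do not support that in general. It holds only in the 50% column, which lies outside the 35% to 40% on which the sample size rests, and only if both are counted as events with none recounted in PCA. If loss is unrelated to need, two hidden events at 30% need imply about 2/0.30 ≈ 7 lost surgical patients.

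A reader might also infer that the bias favours surgery. No refusal, withdrawal or death figures by arm are given, the Discussion expects complication rates to become equivalent, and Step 5 shows equal losses working against surgery.

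There are partial safeguards. Freedom from AF at 12 months is also primary, and procedural complications are a secondary outcome. Crossover is allowed, so a patient who declines thoracotomy may have PCA and stay at risk of a second ablation. These help interpretation but do not settle how this outcome is counted. The contrast between requiring and receiving is mainly Abstract against Methods, and carries little weight alone.

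**Conclusion.** The concern holds in limited form. As worded, the second-ablation outcome puts patients who leave, die or are never ablated on the favourable side, while Table 1 presumes that every first failure is re-treated. The better-documented defect is the asymmetry: a counting rule for failures without a second procedure exists for PCA and not for surgery.

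The size depends on the scenario: two recounted surgical patients in the 50% column, five in the 45% column, and 7 to 10 at the design assumption. These counts assume the uncorrected two-sided z test and no recounting in PCA. The direction is not known. The point merits a change of wording and supporting analyses; it does not show that the planned comparison is invalid.

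**What to change.** 1. Reconcile the Staged surgical ablation group, Percutaneous catheter ablation group and Statistical analysis sections, so that one rule for counting patients without a second procedure applies to both arms. State whether such patients enter the numerator of the z test. This concerns counting only, not how recurrence is treated.
2. Support the z test with the Kaplan-Meier and log-rank methods already planned, applied to time from randomisation to second ablation. Censor withdrawals at last contact and report deaths separately by arm. Counting death as an event would instead create a different, composite endpoint.
3. Add a sensitivity analysis that counts withdrawn, dead and never-ablated patients as failures in both arms. Item 2 cannot replace it: censoring assumes that loss is uninformative, and never-ablated patients who stay in follow-up remain event-free under Kaplan-Meier.

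The cost is a little more analysis work, with no extra patients or visits, and a possibly less favourable or less precise figure.

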### Exclusion criteria

• Patients with paroxysmal AF, defined as a sustained episode lasting <7 days.

• Patients with long-standing persistent AF lasting >1 year.

• Patients for whom cardioversion or sinus rhythm will never be attempted/pursued.

• Patients with AF secondary to a reversible cause.

• Patients with contraindications to systemic anticoagulation.

• Patients with left atrial size ≥55 mm (2-dimensional echocardiography, parasternal long-axis view).

• Patients with LA thrombi as demonstrated by transesophageal echocardiography (TEE).

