### Percutaneous catheter ablation group

One hundred patients will be randomized to PCA and treated according to the protocol of the referring center. In all cases, complete PVI must be at least attempted and confirmed by bidirectional block. The referring investigator can then add any of the current methods of PeAF treatment, including substrate modification with the infusion of isoproterenol to uncover non-PVI triggers and CFAE. Lines can be drawn at the discretion of the investigators. Inducibility of AF at the end of the procedure will be recorded. Cardioversion will be allowed to restore SR.

After the 3-month blanking period, it will be left to the investigator’s preference to refer the patients with PeAF recurrence to a second PCA procedure, surgical ablation, or switch to a rate-control approach. The latter will be counted as a failed repeated procedure.

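### The between-arm tests of the primary outcomes are valid but unadjusted; left atrial diameter, needed in every patient before entry, should be a prespecified covariate

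*Protocol article*

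**What the plan says.** All references are to the Protocol article.

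- **Primary outcomes** (Assessment of recurrence): freedom from AF at 12 months and the occurrence of a second ablation. Both are binary.
- **Tests** (Statistical analysis): χ² for categoric variables; for second procedures, the *z* "test and the odds ratio will be used for differences between proportions of patients receiving repeated procedures in the two groups". Time-to-event curves are compared by log-rank. A P value "< 0.05 will be considered statistically significant". None of these comparisons takes a covariate.
- **Covariates** (same section): they appear only in a Cox model that looks for risk factors for recurrence by stepwise entry. It is not presented as the treatment comparison.
- **Left atrial size** (Exclusion criteria): one listed exclusion is "Patients with left atrial size ≥55 mm (2-dimensional echocardiography, parasternal long-axis view"), so the value has to be known for every patient before entry.
- **Planning figures** (Statistical analysis and Table 1): the sample size assumes that "the success rate of the first procedure will be approximately 70% for the surgical cases and 35% to 40% for the PCA cases". Table 1 then gives power of 99%, 84% and 65% for catheter success of 35%, 45% and 50%.

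**The concern.** A continuous baseline measurement that the trial itself uses to decide eligibility is left out of the treatment comparison. If diameter predicts outcome within the eligible range, two things follow. A chance difference in diameter between a surgical arm of 50 and a catheter arm of 100 shifts the observed effect, and a crude test cannot correct for it. The outcome variation that diameter explains also stays in the error term, in a plan whose least favourable scenario has 65% power.

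The choice is fixed in the article by naming the tests, so it is not merely a detail left to a fuller analysis plan. The timing also matters: adjustment chosen after the data are seen is open to challenge, and a stepwise model does not fill the gap because its content depends on the data.

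**Working it through.** **Inputs from the article.** 100 catheter patients ("One hundred patients will be randomized to PCA") and 50 surgical; surgical success 70%; catheter success 45% or 50% in the less favourable columns of Table 1; significance level 0.05. Sidedness is not stated. Two-sided is assumed because it reproduces the stated power; one-sided gives 99.5/90.7/76.4% and does not.

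**Step 1: reproduce the stated power.** Power = Φ[(Δ − 1.96·s0)/s1], with s0 = √[p̄(1 − p̄)(1/100 + 1/50)] and s1 = √[p(1 − p)/100 + 0.7×0.3/50].

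- 35%: p̄ = 0.467, s0 = 0.0864, s1 = 0.0805; (0.35 − 0.1694)/0.0805 = 2.24; power 98.8% (stated 99%).
- 45%: p̄ = 0.533, s0 = 0.0864, s1 = 0.0817; (0.25 − 0.1694)/0.0817 = 0.99; power 83.8% (stated 84%).
- 50%: p̄ = 0.567, s0 = 0.0858, s1 = 0.0819; (0.20 − 0.1682)/0.0819 = 0.39; power 65.1% (stated 65%).

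So Table 1 gives the power of a crude test, correctly.

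**Step 2: chance imbalance.** SE of the difference in mean diameter = √(1/50 + 1/100) = 0.173 SD. 0.25/0.173 = 1.44, so P(difference of at least 0.25 SD, either way) = 0.149, about 15%. Near 70% success the shift is roughly 0.25 × ln(OR) × 0.7 × 0.3: at OR 1.5, 0.25 × 0.405 × 0.21 = 2.1 points; at OR 2.5, 0.25 × 0.916 × 0.21 = 4.8 points. Averaged over the spread of diameters, the second figure is about 4. The range is therefore about 2 to 4 points.

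**Step 3: power with adjustment.** The prognostic strength of diameter is not in the article, so a range is shown. The simulation used 50 v 100 patients, a standard normal covariate and 6,000 replicates per setting, comparing the crude *z* test with the Wald test of arm in logistic regression on arm and diameter.

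| Fall in odds of success per SD (assumed) | 45% catheter success: crude v adjusted | 50% catheter success: crude v adjusted |
|---|---|---|
| 1.5-fold | 85.9 v 85.6% | 66.7 v 66.0% |
| 2.0-fold | 85.1 v 87.1% | 66.4 v 68.6% |
| 2.5-fold | 85.5 v 89.3% | 66.8 v 72.0% |

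If diameter is not prognostic, the adjusted Wald test loses 1.5 to 2 points. With no treatment effect, the crude test rejected in 5.4 to 5.8% of trials and the diameter-adjusted test in 4.7 to 5.3%, so the gain is not bought with false positives.

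**Step 4: cross-checks.** A linear risk-difference model with robust standard errors gave gains of about 0 points (not prognostic), 0.5 to 2 (1.5-fold), 2.5 to 4.5 (2.0-fold) and 4 to 7 (2.5-fold). Putting Δ/√(1 − R²) in place of Δ in the formula of Step 1, with R² assumed:

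| R² | 0 | 0.02 | 0.05 | 0.10 | 0.15 |
|---|---|---|---|---|---|
| 45% catheter success | 83.8% | 84.6% | 85.7% | 87.5% | 89.4% |
| 50% catheter success | 65.1% | 66.0% | 67.4% | 69.9% | 72.4% |

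The three methods agree on direction and rough size. None brings the 50% scenario to 80%.

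**The case against.** **Nothing is stated wrongly.** In a randomised trial the *z* and χ² tests are valid, and their error rate already allows for chance imbalance. This stands. A reader might infer that the planned tests are biased; they are not.

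**The prognostic strength is assumed.** The article gives no reason for the 55 mm limit and no evidence that diameter predicts outcome below it. This stands too. It rules out the stronger reading that adjustment is free and always raises power: the table shows no gain at 1.5-fold, and there is a small loss if diameter is not prognostic.

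**The harm is modest.** A 15% chance does not make imbalance likely. A shift of 2 to 4 points is small against the standard error of the comparison, √(0.7×0.3/50 + 0.5×0.5/100) = 8.2 points. This stands.

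**The gain does not reach every primary outcome or the main planning case.** At 35% the power is already 99%. The article expects final sinus rhythm to be similar in the two arms, so the power figures above do not carry over to 12-month freedom from AF. They bear on first-procedure success and, through Table 1, on second procedures. Those also depend partly on investigator preference, which may weaken the link with diameter. For the rhythm outcome, what remains is the correction of imbalance.

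**Centre.** A reader might go further and ask for adjustment for centre, or for re-stratified randomisation, because catheter patients are "treated according to the protocol of the referring center". The article does not support that. The number of centres is not given. The stated variation in technique concerns the catheter arm only, since the first surgical procedure is held to one device and one access, so it behaves more like a treatment-by-centre difference than a shared prognostic factor. Investigator discretion over second procedures does exist in both arms, but its size is unknown. Centre terms can also cost power. With 20 centres that have no effect and a 1.5-fold diameter effect, the fully adjusted risk-difference test has 80.7% v 84.4% crude at 45% catheter success, and 60.7% v 66.5% at 50%. With 5 centres acting only in the catheter arm it gains nothing (81.4 v 81.6%; 65.3 v 65.4%). Changing the randomisation of a trial already recruiting is a separate trade-off.

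**Conclusion.** The point holds as a missed improvement, not an error. The planned comparisons are crude, a continuous baseline covariate is at hand for every patient, and prespecifying it would correct for chance differences in diameter.

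The size is modest and conditional: about 2 to 5 points of power in the 45% and 50% columns of Table 1 if the odds of success fall 2.0- to 2.5-fold per SD, about nil at 1.5-fold, and a loss of up to about 2 points if diameter is not prognostic. These figures assume a two-sided 5% test, no dropout, a normally distributed diameter (the true range is cut off at 55 mm) and a prognostic strength that the article does not give. Adjustment does not rescue the 50% scenario, and no claim is made for centre.

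**What to change.** Name the following as the primary between-arm analysis of each binary primary outcome, before any comparison by arm is seen:

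1. Logistic regression of the outcome on arm and left atrial diameter, entered as a continuous variable from the eligibility echocardiogram, by intention to treat.
2. The effect reported as the standardised (marginal) risk difference with its 95% CI. An adjusted odds ratio is conditional on diameter and does not estimate the same quantity as the planned crude odds ratio; the standardised difference avoids that mismatch.
3. The crude *z* or χ² test kept as a supporting analysis.
4. The stepwise Cox model kept for its stated purpose, the search for risk factors, and not used to estimate the treatment effect.

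Add centre only if centres are few or were used to stratify the randomisation.

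The cost is a few lines in the analysis plan, one extra model parameter, a short standardisation step, and the possible loss of up to about 2 points of power if diameter proves not to be prognostic. No new visit or measurement is needed, and the randomisation stays as it is.
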